### Hypothesis

Adolescents who receive a multi-component intervention targeting screen time and sedentary behaviours will show a significant reduction in screen sedentary time (SST) and Non screen sedentary time (NSST) compared to those who do not receive the intervention.

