### Baseline data collection

A self-administered questionnaire will be used to gather the demographic data, which includes information like age, gender, class, section, address, contact information, and the parents’ or guardians’ occupations. The study participants will be asked about their screen- and non-screen-based sedentary time as well as their physical activity. Anthropometric measurements like height, weight, waist and hip circumference will be collected using standardized techniques.
^
31
^

Following the collection of baseline data, the schools selected for intervention will receive the multi-component modular intervention. Three sessions at two monthly intervals will be conducted in these schools. (Baseline, second month and fourth month) Both groups will complete the questionnaires at baseline, and two, four and six months of follow-up. Anthropometric measurements will be taken at baseline and sixth month of follow-up) Outcome will be assessed at each point of time in both intervention and control arm students. Confidentiality and anonymity will be maintained throughout the study (
Figure 1).

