### Outcome variables

1.Mean screen sedentary time (SST) and non-screen sedentary time (NSST)2.Level of physical activity3.Association of BMI, waist circumference hip circumference and waist height ratio with screen sedentary time and non-screen based sedentary time4.Difference in the mean SST and mean NSST between the intervention and control group

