### Data management

Utilizing IBM SPSS (Statistical Package for Social Sciences) Statistics for Windows Version 25.0, the gathered data will be coded, inputted, and analyzed. Armonk: IBM Corporation.
^
33
^ The proformas will be checked for completeness and the participant will be contacted for any missing information. The data will be kept confidential and protected using encryption.

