### Data analysis

Proportions will be used to express the results. The interquartile range (IQR) and standard deviation (SD) associated with summary measures like mean and median will be reported for continuous variables. ITT analysis—intention to treat—will be used. The data will be represented by suitable tables and figures. The chi-square test will be used to compare variables between intervention and control groups. The baseline and post-intervention values across the intervention and control groups will be compared using the Mann-Whitney U test for non-normal data. (ST, SST, NSST) For data following normal distribution (WC, HC) independent t-test will be used and p < 0.05 will be considered to be statistically significant. Repeated measures of ANOVA will be used to compare the change scores (ST, SST, NSST) within the intervention and control groups and ’a p-value less than < 0.05 will be considered statistically significant.

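### The only analysis that uses the repeated visits tests change within each arm, so it does not test the between-arm hypothesis

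*Protocol article*

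**What the plan says.** The trial's question is comparative. The Hypothesis section expects that adolescents given the intervention "will show a significant reduction in screen sedentary time (SST) and Non screen sedentary time (NSST) compared to those who do not receive the intervention". The fourth item under Outcome variables is "Difference in the mean SST and mean NSST between the intervention and control group". The Sample size calculation section is built on a 0.9-hour difference in mean SST between the arms.

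The data are longitudinal: "Both groups will complete the questionnaires at baseline, and two, four and six months of follow-up" (Baseline data collection).

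The Data analysis section gives two methods for SST and NSST:
- Between arms: "The baseline and post-intervention values across the intervention and control groups will be compared using the Mann-Whitney U test for non-normal data". ST, SST and NSST are named as the variables concerned.
- Over time: "Repeated measures of ANOVA will be used to compare the change scores (ST, SST, NSST) within the intervention and control groups", with p below 0.05 called significant.

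On the analysis set, the same section says "ITT analysis—intention to treat—will be used". On missing data, the Data management section says "The proformas will be checked for completeness and the participant will be contacted for any missing information".

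**The concern.** A test of change over time inside one arm asks whether that arm moved. It does not ask whether the two arms moved differently. Repeated questioning, regression to the mean and the school calendar can shift both arms, so a significant fall in the intervention arm is not evidence of an intervention effect, even when the control arm's fall is not significant. Because the ANOVA carries its own significance threshold, its result could be presented as the trial's finding.

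There is a second, smaller issue. Classical repeated-measures ANOVA uses only pupils with every visit present unless missing values are imputed. A pupil absent on one questionnaire day would then leave the analysis, which sits poorly with the stated intention-to-treat approach.

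**Working it through.** **1. What the sample size is for.** Inputs from the Sample size calculation section: d = 0.9 h, σ = 3.025 h, z = 1.96 and 0.84, design effect 2, loss 10%.
- n = 2(1.96 + 0.84)² × 3.025² / 0.9² = 2 × 7.84 × 9.1506 / 0.81 = 177 per arm, close to the stated 180. (The formula as printed omits the square on the z sum; the stated 180 matches the squared form.)
- 180 × 2 = 360, and 360 / 0.90 = 400.

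The stated figures reproduce, and they are for a between-arm difference in means.

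**2. Which planned analysis estimates that difference.**
- The repeated-measures ANOVA is stated as within the groups, and no arm-by-time term is named. The same paragraph uses a different word, across, for the between-arm comparison, so the literal reading is within-arm testing. It does not estimate the arm difference.
- The Mann-Whitney U test does compare the arms. It is a rank test on values at a time point, with no baseline adjustment and no use of the trajectory, and it does not estimate a difference in means.
- The article does not say which of the two decides efficacy.

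**3. What reading the arms side by side would cost.** Assume that both arms change equally, that the arms are independent, and that each within-arm test has power p. The chance of significance in the intervention arm but not in the control arm is p(1 − p).

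| Assumed p | p(1 − p) |
|---|---|
| 0.05 (no change in either arm) | 4.75% |
| 0.20 | 16% |
| 0.50 | 25% (maximum) |
| 0.80 | 16% |

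To see which common shift gives such values, take a simple before-after comparison on 360 pupils per arm, with σ = 3.025, design effect 2 and an assumed baseline-to-follow-up correlation ρ = 0.5. Then SE = σ√(2(1 − ρ)) × √(2/360) = 3.025 × 0.0745 = 0.225 h, and p = Φ(shift/SE − 1.96).
- Shift 0.20 h in both arms: p = 0.142, misleading pattern in 12%.
- Shift 0.30 h: p = 0.265, pattern in 19.5%.
- Shift 0.45 h, half the planned effect: p = 0.514, pattern in 25%.

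**4. Complete cases.** Pupils absent at baseline are excluded (Exclusion criteria), so three follow-ups matter. Assume that a share m is absent at each, independently. The complete share is (1 − m)³ of 400. Power for the 0.9-hour contrast uses n/2 for the design effect: Φ(0.9 / (3.025√(2/(n/2))) − 1.96).

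| m | Complete pupils per arm | Left out | Power, complete cases | Power, all seen at 6 months |
|---|---|---|---|---|
| 2% | 376 | 5.9% | 82% | 84% |
| 3.5% | 359 | 10.1% | 80.5% | 83% |
| 5% | 343 | 14.3% | 79% | 83% |
| 10% | 292 | 27.1% | 72% | 81% |

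The documents give no absence rate per visit, so every m is an assumption.

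**The case against.** Several stronger readings are tempting, and the document does not support them.

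- *A reader might infer that the plan never compares the arms.* It does. The Mann-Whitney U test sets SST and NSST in one randomised arm against the other, so the follow-up data are not wasted for the trial's question. What stands is that this test is unadjusted for baseline, leaves the trajectory unused and does not match the powered quantity.
- *A reader might take 25% as the trial's false-positive rate.* The protocol states no rule that efficacy follows from significance in one arm only. The figure is the maximum of p(1 − p) under such a rule and an assumed power.
- *A reader might say that the plan drops every pupil who misses a visit.* No sentence says so. That is how the classical method works without imputation, and an analysis plan not shown here may deal with it. The Study participants section also expects little or no loss, although its reason is that pupils stay at the school, which does not rule out absence on a visit day. The 10% allowance was made for a two-group comparison, which does not need every visit, so it is not a strict yardstick for the complete-case losses.
- *The word within may be loose* for an ANOVA with a group factor. This is possible, but the paragraph's own contrast between across and within argues against it, and the text should then say so.
- *A reader might object that ANOVA is applied to variables the plan calls non-normal.* This argument is not relied on. The ANOVA is on change scores, and the mixed model proposed below also assumes normal residuals.

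**Conclusion.** The point holds in this form: the only method stated for the repeated visits is within-arm inference at p < 0.05, and it does not address the comparison that the hypothesis, the fourth outcome and the sample size all require. This rests on the article's wording alone. The between-arm test that does exist is a weaker match to the 0.9-hour mean difference, and the article leaves open which result counts.

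The sizes are conditional. A misleading pattern in up to 25% of trials with equal change needs both a side-by-side reading and within-arm power near 50%. Complete-case losses of 14% or 27% need no imputation and independent absence of 5% or 10% per follow-up. The sample size is not affected.

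**What to change.** Replace the within-arm ANOVA with one linear mixed model for each of SST, NSST and ST over the 2-, 4- and 6-month visits:
- fixed effects for arm, visit, arm-by-visit and the baseline value;
- random intercepts for school and for pupil;
- small-sample degrees of freedom suited to 20 schools.

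Name the six-month between-arm contrast, a mean difference in hours with its 95% confidence interval, as the test of effect. Report within-arm changes descriptively, without p-values. If the Mann-Whitney comparison is kept, label it supportive.

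The model uses every available follow-up questionnaire, so a pupil with a baseline value and at least one follow-up stays in the analysis. It also carries the school clustering and estimates the quantity on which the sample size rests.

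The cost is a change of analysis wording. The Current status section says that recruitment has not begun, so the change can be made before any data exist. It needs no more pupils, schools or visits. The Ethical considerations section requires changes made after the study starts to go back to the ethics committee, which is a reason to act now.

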### Implications

A comprehensive school-based modular intervention with an active behavioural change component like the one utilized in this study can have cumulative advantages by reducing screen- and non-screen-based sedentary time, encouraging physical activity, and promoting quality sleep to mitigate each factor’s individual effects on adiposity measurements in teenagers. It can be effective in promoting healthier habits and reducing the negative impacts of excessive screen time on academic performance, physical health, and overall well-being.

### Ethical considerations

The Institutional Ethics Committee (IEC) at Kasturba Medical College, Mangalore has approved the study protocol.

If changes are made to the protocol after the commencement of the study, it will be resubmitted to the IEC for approval.

The trial has been registered with the Clinical Trial Registry-India (CTRI) (REF/2023/04/066280).

Required permissions will be obtained from the block educational officer and the school administration.

Written parental approval and informed assent will be obtained from the participants. The participant information data will be handled with the utmost confidentiality.

### Data monitoring

An interim analysis will be carried out after 3 months from the commencement of the study. There is no known adverse effect associated with this study. There will not be any committee formed for data monitoring. The selected schools in the control arm will be offered the modular intervention at the end of the final data collection.

### Dissemination

Presentations at scientific meetings and publications will be used to publicize the study’s findings. As stated in the methodology, we will report the study’s flow and results using the CONSORT principles. The Standard Protocol Items: Recommendations for Interventional Trials (SPIRIT) Guidelines are used to report the study’s protocol. As a result of the research data’s potential to compromise participants’ anonymity and the fact that they contain personal information, the IEC guidelines of the study institute forbid sharing research data with any other organization. However, the information can be obtained from the associated author upon personal request and with sufficient cause.

### Current status of the study

The study has not started recruiting participants.

## Data availability

No data are associated with this article.
